## Abstract

**Background:**

Up to two-thirds of dementia care is provided by family caregivers who often experience high burden, little support and adverse health outcomes. Enabling and supporting family caregivers to provide care at home prevents early institutionalisation of the person with dementia and alleviates the economic burden of dementia in the long term. General practitioners (GPs), as the first point of contact, have a key role in identifying and managing burden and care needs of family caregivers. However, in routine care, this opportunity is often limited by time constraints and even if caregiver needs are recognised, detailed information about regionally available support and advice on healthcare services is often lacking.

**Methods:**

This is a cluster randomised, controlled trial investigating the clinical use and cost-effectiveness of a digitally supported care management programme for caregivers of people with dementia (PwD). Five hundred family caregivers will be randomised at GP offices, specialist practices and memory clinics, with about *n*=250 participants per arm. Participants are eligible if they are the primary family caregiver of a PwD, are at least 18 years of age and provide informed consent. Participants in the intervention group will receive an individualised care management plan, which will be carried out by qualified study nurses in collaboration with the treating GP. All participants will receive a baseline assessment and a 6-months follow-up assessment. Participants in the wait-list control group will receive usual care. Starting at the 6 months’ follow-up, the former controls will also receive an individualised management plan. Primary outcomes are the number of unmet needs (incl. the Camberwell Assessment of Need for the Elderly, CANE) and health-related quality of life (EQ-5D-5L) at 6 months. Secondary outcomes include caregiver burden (Zarit Burden Interview, ZBI), social support (Lubben Social Network Scale, LSNS), the use of medical and non-medical services (Questionnaire for the Use of Medical and Non-Medical Services, FIMA) and resource utilisation (Resource Utilisation in Dementia, RUD). The primary analysis will be based on intention-to-treat. Between- and within-group analyses and a cost-effectiveness analysis will be conducted to estimate the effect of the tablet PC-based care management programme. This trial is funded by the German Federal Joint Committee (G-BA) Innovation Fund.

**Discussion:**

The findings of this trial will be useful in informing and improving current healthcare system structures and processes to support family dementia caregivers within routine care practices.

**Trial registration:**

ClinicalTrials.gov NCT04037501. Registered on 30 July 2019.

**Supplementary Information:**

The online version contains supplementary material available at 10.1186/s13063-021-05290-w.

## Background

It is estimated that about two-thirds of the 1.6 million people with dementia (PwD) living in Germany are cared for at home by a relative [1]. Family caregivers are essential to the quality of life of the care recipients [2]. Caring for a relative is associated with a multitude of time- and resource-intensive challenges [3–5]. Family caregivers often report that the dementia-related progressive loss of memory and physical, motor and social functions, and the manifestation of neuropsychiatric symptoms, such as agitation, depression, apathy, aggression and delusions, render caring for a person with dementia extremely stressful [6, 7].

Recent reviews confirm that family caregivers of PwD experience increased physical, psychological, emotional and social stress which, in the long term, can lead to health problems in the caregivers who are sometimes referred to as the invisible second patients [2]. Deterioration of caregivers’ health can lead to an early institutionalisation of the PwD [6, 7]. Family caregivers of people with dementia are likely to suffer from a range of health problems, such as depression, anxiety and physical illnesses [8, 9], as well as other negative conditions, such as social isolation, financial strain and poor quality of life [8, 10]. The early identification of care needs and the associated initiation of care services (e.g., visits to the doctor, joining self-help-groups, physiotherapy, or vacation replacements) can ameliorate perceived stress and prevent the occurrence of health problems among family caregivers [10, 11].

According to Murray, a need refers to a condition or experience of a problem combined with the desire to change it [12]. Based on this definition, unmet care needs of family caregivers arise from (a) the perception of a problem and (b) the simultaneous realisation that this problem is not addressed adequately by healthcare services, resources, or support services. Recent systematic reviews of qualitative and quantitative studies examining unmet care needs show that family caregivers of PwD frequently report unmet needs regarding their insufficient knowledge about dementia, available services, social, legal and financial matters, social integration and their own physical and mental health [13, 14].

Cross-sectional data from a general practitioner (GP)-based, cluster randomised, controlled intervention study conducted by our group [15] showed that 76% of family caregivers had at least one unmet care need in one of the abovementioned areas. Furthermore, the care needs of family caregivers arose from two sources: either from the care responsibilities for the PwD or from the personal needs of the family caregiver [16]. To ensure that family caregivers receive the support and care they need, regardless of where they live, their educational and socioeconomic status, problems need to be identified early and managed efficiently. Time constraints, skilled labour shortage, lack of information transfer between healthcare professionals regarding available services and lack of services in rural areas render the use of digital information and support systems essential to identify unmet needs of caregivers and appropriately address each of those in an individualised care management plan. Practitioners in general medicine have a key role in this process, because they are usually the primary healthcare contact for family caregivers. GPs often know the family caregivers for many years and can, therefore, identify changes in strain and stress as well as imminent care needs. This requires, however, that healthcare professionals not only recognise and identify unmet care needs of family caregivers of PwD but also inform them about appropriate regional care offers and provide advice on how they can access and receive them. For this, effective identification of caregiver needs and communication and collaboration between healthcare professionals need to be optimised digitally. The need for digital innovations in healthcare has been further amplified by the present COVID-19 pandemic which renders the provision of dementia services difficult if not impossible to maintain in the current healthcare structures. Given that healthcare services are often scarce, not known or not available in rural areas, the German federal state of Mecklenburg-Western Pomerania (MV) qualifies for testing the effectiveness of a digitally supported care management programme to improve healthcare services for family caregivers of people with dementia.

The programme will be supported by a tablet PC-based care management system (CMS) which will aid in generating and conducting an individualised care management plan for family caregivers. First, the CMS will identify unmet needs of family caregivers of PwD on the basis of a standardised self-administered assessment and then generate an individualised care plan based on predefined algorithms triggered by the caregivers’ answers. Qualified study nurses in collaboration with the treating GPs will then carry out the individual care plan as part of the care management programme.

This trial has been designed to assess the clinical use and cost-effectiveness of a digitally supported care management programme, based on recent research suggestions [16], own research [17–20], clinical guidelines [21] and current clinical practice in Germany.

## Methods

### Trial objectives

The primary objective is to examine the effectiveness of a digitally supported care management programme to reduce unmet needs and improve quality of life in caregivers for PwD between a group receiving the intervention and a wait-list group receiving usual care. The secondary objectives are to assess cost-effectiveness of the programme and to examine whether the care management programme is associated with improvements in participants’ perceived burden, social support and use of services and resources.

### Study design and sites

This trial is a multisite, longitudinal, cluster randomised, controlled interventional trial (cRCT) with two data assessment points (baseline assessment and six months follow-up) in a wait-list control group design. The intervention will be initiated in GP offices, specialist practices and memory clinics across the German federal state of Mecklenburg-Western Pomerania.

Throughout the study, an advisory board will convene at least annually. The advisory board will oversee the conduct of the study and provide feedback. Family caregivers of PwD, representatives of the German Alzheimer Society, GPs and specialists as well as their practice staff will be involved in the planning, development, implementation and evaluation of the study.

### Recruitment

GPs and memory clinics in the federal state of MV will be contacted and invited to participate as recruitment centres. The recruitment began in October, 2020. Subsequently, caregivers will be recruited in participating GP offices and specialist practices. Participant recruitment is planned for 12 months. The expected progress of the trial is shown in Fig. 1.

**Fig. 1 Fig1:**
[figure not shown]
CONSORT 2010 flow diagram. The expected progress of the study

### Ethical approval

Ethical approval has been obtained from the Ethical Committee of the University Medicine Greifswald (Registry number BB 120/2019) and the Ethical Committee of the University Medicine Rostock (Registry number A2020/0013).

### Study population and selection criteria

Family caregivers are eligible to participate in the study if they are above the age of 18, the caregiver of a PwD living at home, are able to speak German sufficiently to complete the baseline assessment and give written informed consent. Potential participants will be excluded if they are not living in the study region (Federal State of Mecklenburg-Western Pomerania), do not provide written informed consent, are unable to complete the self-administered baseline assessment and/or cannot be interviewed.

### Intervention

The conceptional framework of this intervention is the evidence-based Dementia Care Management as conducted and adapted in several primary care studies [17, 18, 22–24]. It consists of (i) an assessment of the health and social status of the participant at the time of recruitment, (ii) a comprehensive needs assessment at the time of recruitment, (iii) a systematic, written feedback for the participant’s treating GP, (iv) a study nurses led completion of the needs assessment at the participant’s home shortly after recruitment, (v) a collaborative consultation between the participant’s GP and the study nurse in which recommendations for treatment and care for the participant are coordinated and (vi) continuing support in reducing the participant’s unmet needs identified in the needs assessment.

The entire programme is delivered by specifically qualified study nurses in co-operation with participants’ GPs and/or specialists and will be supported by a tablet PC-based CMS. The system is a rule-based expert assessment and documentation support system that matches individual participant characteristics to recommendations for treatment and care. The system supports the identification of a participant’s unmet needs, selects corresponding participant-specific interventions and integrates these into an individualised care management plan. The CMS has been proven to support the systematic identification of unmet needs and to improve the selection of specific intervention modules [16, 25]. These will then be systematically addressed by the study nurses in co-operation with the treating GP. The CMS on its own does not replace any provisions offered by healthcare providers and is used exclusively as a tool to effectively support the individual care management programme.

### Outcomes

The primary objective is to determine the effectiveness of a digitally supported care management programme to reduce unmet needs and improve health-related quality of life in caregivers for PwD in the primary care setting.

Primary outcomes are (a) number of unmet needs and (b) health-related quality of life. They are measured as follows:
The number of unmet needs will be assessed with a standardised assessment which is part of the tablet PC-based CMS and addresses the participants’ medical needs, home care needs, psychosocial needs and needs connected to the caregiver role. This needs assessment includes the Camberwell Assessment of Need for the Elderly (CANE) [26, 27].Health-related quality of life will be assessed using the EQ-5D-5L [28, 29]. This instrument comprises five dimensions, namely, mobility, self-care, usual activities, pain/discomfort and anxiety/depression. Each dimension has five levels varying from no problems to extreme problems. Each level corresponds to a 1-digit number that expresses the level selected for that dimension ranging from 1 to 5 with higher numbers indicating more severe problems. The digits for the five dimensions can be combined into a 5-digit number that describes the participant’s health status.

Secondary outcomes of this trial are the following: (a) caregiver burden, (b) social support, (c) use of medical and non-medical services and (d) the use of resources in dementia. They are measured as follows:
Informal caregiver burden will be assessed using the seven-item version of the Zarit-Burden Interview (ZBI-7). The short version ZBI is a caregiver self-report measure to examine burden which is associated with functional/behavioural impairments in the social, psychological and physiological context and home care situation [30]. It contains seven items using a five-point scale. Response options range from 0 (never) to 4 (nearly/always). Total scores range from 0 indicating no burden to 28 indicating severe burden.Social support will be assessed using the Lubben Social Network Scale (LSNS-6) [31]. This scale is a self-report measure of social engagement including family and friends on a six-item scale. Total scores range from 0 to 30 with an equally weighted sum of the six items. The family and friends subscales include questions regarding the number of friends and family one has regular contact with as well as availability for help and support in private matters [32]. High scores indicate strong social networks.The use of medical and non-medical services includes the Questionnaire for the Use of Medical and Non-Medical Services in Old Age (Fragebogen zur Inanspruchnahme medizinischer und nicht-medizinischer Versorgungsleistungen im Alter, FIMA) [33]. The FIMA examines socioeconomic variables and other medical factors to determine health-related costs.The use of resources in dementia will be assessed using the Resource Utilisation in Dementia (RUD) [34].

The primary and secondary outcomes except the FIMA and RUD will be assessed at baseline (T_0_) and at the 6 months follow-up (T_6_). The FIMA and RUD will be assessed at the 6 months follow-up only (T_6_).

Data assessment tools for these dimensions were selected based on either their recommendation by the EU Joint Programme in Neurodegenerative Research (JPND) Working Group on Longitudinal Cohorts or common use in larger German trials such as IDemUck [35], DelpHi-MV [17, 18, 22], intersec-CM [23], or DemNet-D [36]. These instruments are validated and will allow comparability with German and international studies. An overview of the trial and assessment points of the outcome measures is provided in Fig. 2 and the SPIRIT 2013 checklist is provided in Additional file 1.

**Fig. 2 Fig2:**
[figure not shown]
GAIN trial design

### Sample size

The estimated sample size for the study is *n*=504 participants and is based on power calculations with the NCSS programme PASS 2019 [37]. Expecting a drop-out of 30% within the study period, we assume that data of *n*=352 subjects (*n*=176 per group) will be available at the end of the study. Both groups are planned to consist of 22 clusters, each providing *n*=8 participants on average. Thus, we will be able to show a significant difference between the mean numbers of unmet needs in both groups of at least one standard deviation with a power of 80%. In this set of assumptions, the intra-class correlation is set to 0.1. The coefficient of variation of cluster sizes (COV) is 0.63, which allows variance in cluster sizes between 8 and 37. The hypothesis is tested with a one-sided test at a significance level of *α*=0.05.

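### The sample-size inputs give 80% power for about 0.38 SD in unmet needs, not for the one SD that the protocol states

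*Protocol article*

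**What the plan says.** All of this is in the Sample size section of the protocol article. It plans to recruit 504 caregivers, allows for 30% drop-out, and expects that "data of *n*=352 subjects (*n*=176 per group) will be available at the end of the study". On the structure it says "Both groups are planned to consist of 22 clusters", with an average of 8 participants each. The intra-class correlation is 0.1. The coefficient of variation of cluster sizes is 0.63, which the text links to sizes from 8 to 37. The test is given as a "one-sided test at a significance level of *α*=0.05". From these it concludes that the trial can show a "significant difference between the mean numbers of unmet needs in both groups of at least one standard deviation with a power of 80" per cent.

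The article gives no other target difference for either primary outcome, and no SD for the number of unmet needs.

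**The concern.** One standard deviation is a very large difference to need 352 analysed participants, even after allowing for clustering. The section prints every input required to derive the detectable difference, so the result can be checked directly, and it does not follow from those inputs.

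This sentence is the whole of the article's justification for recruiting 504 caregivers. If the effect size is misreported, a reader cannot tell what difference the trial was built to find or whether it is relevant and realistic. If one SD really was the target, the planned number is left unexplained.

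**Working it through.** **Inputs (Sample size section).** k = 22 clusters per arm; mean size m = 8; analysed n = 176 per arm; ICC = 0.1; coefficient of variation CV = 0.63; one-sided alpha 0.05 (z = 1.645); power 80% (z = 0.842).

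**Figures that reproduce.** 22 × 8 = 176 per arm, and 2 × 176 = 352. For drop-out, 504 × 0.7 = 352.8, and 352 / 0.7 = 503 against the stated 504.

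**Detectable difference.**

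- Design effect for unequal clusters: 1 + [(1 + CV²)m − 1] × ICC = 1 + [(1 + 0.3969) × 8 − 1] × 0.1 = 2.0175.
- Effective n per arm: 176 / 2.0175 = 87.2.
- Standard error of the difference, in SD units: √(2 / 87.2) = 0.151.
- Normal approximation: (1.645 + 0.842) × 0.151 = **0.376 SD**.
- Non-central t with 2 × (22 − 1) = 42 df: **0.383 SD**.
- With the relative-efficiency correction instead, the design effect is 1.887 and the results are 0.364 (normal) and 0.370 (t).

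The ratio of stated to derived difference is 1 / 0.376 = 2.66, and runs from 2.61 (1 / 0.383) to 2.75 (1 / 0.364).

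**Power at one SD.** Under the normal approximation, 1 / 0.1514 − 1.645 = 4.96, so power is above 99.999%. The t version on 42 df agrees.

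**What one SD would need.** The normal formula gives 2 × 2.487² × 2.0175 = 24.9 caregivers per arm, but it is unreliable with so few clusters. Non-central t on 2(k − 1) df, with clusters of 8, gives:

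| Clusters per arm | Caregivers per arm | Power, design effect 2.018 | Power, design effect 1.887 |
|---|---|---|---|
| 3 | 24 | 64% | 67% |
| 4 | 32 | 79.9% | 82% |
| 5 | 40 | 89% | 91% |

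So 4 to 5 clusters (32 to 40 caregivers) per arm are needed. The planned 176 is 176/40 = 4.4 to 176/32 = 5.5 times that.

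**Can another reading give one SD?** Detectable difference at 80% power:

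| Variant | SD |
|---|---|
| No clustering, one-sided | 0.27 |
| Equal clusters (design effect 1.70), one-sided | 0.35 |
| Printed inputs, but two-sided | 0.42 (normal), 0.43 (t) |
| ICC 0.3, CV 0.63, one-sided | 0.53 |
| ICC close to 1, one-sided | 0.89 |
| In units of the SD of cluster means, one-sided | 0.75 |

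No variant with the stated one-sided alpha reaches one SD. A two-sided test with ICC close to 1 comes to 1.00, but that contradicts two printed inputs.

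**Cluster-size range.** Mean 8 and CV 0.63 imply an SD of cluster size of 8 × 0.63 = 5.04. If the smallest cluster is 8 and the mean is 8, every cluster has size 8 and the CV is 0. A range of 8 to 37 therefore does not fit a mean of 8, so at least one cluster-size figure is misreported.

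**The case against.** The best defence is that the error is harmless. The trial is more sensitive than it claims, and the one-SD figure enters no analysis or decision rule: the Statistical analysis section defines success as a significant one-sided coefficient for study group. That stands, and it limits the consequence to the justification of the sample size and what readers understand by it.

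A second defence is that the phrase "at least one standard deviation with a power of 80" per cent only sets a floor, so larger effects are covered too. This does not help. The smallest difference with 80% power is about 0.38 SD, and at one SD the power is practically 100%.

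A third is that an article condenses a fuller protocol. Condensation can explain a missing SD or a missing figure for EQ-5D-5L, and neither is held against the plan here. It cannot explain a printed result that disagrees with the printed inputs.

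Three stronger readings are tempting, and the document does not support them:

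- **That a null result would exclude only effects of one SD or more.** What a null result excludes depends on the confidence interval obtained, not on the planned difference.
- **That the trial is about seven times too large, because 3 to 4 clusters per arm would do.** That rests on the normal approximation, which fails with so few clusters. By the cluster-level t, 3 clusters are not enough, and the factor is 4.4 to 5.5. Even this applies only if one SD was truly the target.
- **That 0.38 SD must simply be written in.** That assumes all other inputs are correctly reported, which the cluster-size range puts in doubt.

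**Conclusion.** The stated detectable difference is wrong. With the inputs as printed, 80% power corresponds to 0.36 to 0.38 SD depending on the formula, so the stated figure is too large by a factor of about 2.7. The error understates the trial's sensitivity; nothing here shows that the sample is too small.

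The result rests on an unadjusted two-arm comparison of means in the cluster design described in the Sample size section. The planned analysis also adjusts for the baseline value, which this calculation does not credit. The conclusion does not depend on the choice of design-effect formula, on normal versus t, or on sidedness alone.

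The source of the error cannot be identified from the article. One possibility is that a difference of one unmet need was meant. Under the printed inputs that has 80% power if the SD is 1 / 0.383 = 2.61 to 1 / 0.376 = 2.66 needs (up to 2.75 with the relative-efficiency correction). The article gives no SD, so this is only an illustration.

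**What to change.** Retrieve the PASS 2019 run and reconcile its inputs and output with the Sample size section, including the mean cluster size, the coefficient of variation and the range of 8 to 37. Then do one of two things:

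- Replace the one-SD sentence with the difference that the confirmed inputs deliver. If the printed inputs stand, that is about 0.38 SD, unadjusted, at 80% power and one-sided alpha 0.05.
- If a raw difference such as one unmet need was intended, state that difference and the SD assumed for it.

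If the printed inputs stand, the cost is a text correction with no change in sample size. If the check shows that an input was misreported, the detectable difference must be recalculated from the corrected value before the text is settled.
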